##### Patient outcome analysis

HRQL will be assessed with the EQ-5D-5L questionnaire at baseline, 6, 18, and 52 weeks or if an early endpoint is reached. The EQ-5D-5L is applied to score a patient’s health status, which is subsequently transposed in QALY’s by applying existing Dutch time trade-off based utility algorithm.

##### Missing HLQ data

When missing values concerning out-of-hospital care consultations are encountered, a value of 0 will be assumed if the questionnaire was otherwise completed. If unrealistic volumes of care are reported or assumed, we will seek to verify information by contacting patients or their care providers and/or estimated volume of care based on group averages.

#### Budget impact analysis (BIA)

##### General considerations

A BIA will be designed and executed in accordance with the International Society for Pharmacoeconomics and Outcomes Research (ISPOR) guidelines [29]. The analysis will be patient based, covering relevant health care costs observed during the 52 weeks study period. The main focus will be on the reduction of expenditures for IVIg medication related to the combined treatment. Analyses will cover relevant health care costs observed, such as continued IVIg infusions and related home care in the event of a relapse requiring treatment, during the follow-up period. Based on trial results, different remission rate scenarios will be considered including a sensitivity analysis around these confidence intervals.

##### Cost-analysis

For the BIA current unit costing guidelines for costing in health care will be applied as previously described. Budget impacts will be expressed in millions of Euros.

#### Interim analyses {21b}

Interim efficacy analyses will not be performed. An independent data and safety monitoring board (DSMB) will perform interim safety analyses, to ensure that the combination of IVIg and IVMP does not cause any undue risk for the patient. These interim analyses will be performed after enrolment of 20 and 60 patients, after and if 20 patients reach a preliminary endpoint during treatment period, in case of a mortality and at the discretion of principal/local investigator. Statistical stopping boundaries are not pre-specified. DSMB recommendations are sent to the PI of the study. If the PI partly rejects (part of) the DSMB’s recommendations, PI will provide the DSMB with a written explanation of his decision and supporting rationale within 2 weeks. If the DSMB has recommended that the study should be stopped but the PI decides to continue the study, the investigator will immediately inform the METC, the Board of Directors, the head of the department and all concerned regulatory authorities of its decision to continue the study despite the DSMB’s recommendation.

#### Methods for additional analyses (e.g. subgroup analyses) {20b}

We will not perform additional analyses.

#### Methods in analysis to handle protocol non-adherence and any statistical methods to handle missing data {20c}

In the ITT analysis, all randomised patients will be analysed in the treatment group to which they were originally allocated, irrespective of potential eligibility deviation, unblinding, non-adherence or other deviations from protocol. In the PP analysis, patients will be analysed who were included in accordance with the study protocol and who completed the treatment originally allocated. Patients in whom protocol deviations occurred will be excluded from the per protocol population, with the exception of the following deviations: patients having missed one IMP and/or IVIg administration, patients who receive their treatment out of window (up to 7 days) or patients with deviations on an infusion-administration level (i.e. partial IMP or IVIg administration (single infusion), IMP administration infused faster than the required 1 h).

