## Trial design {8}

The OPTIC trial is an international, multicentre, randomised, double-blind, placebo-controlled, parallel group superiority trial with two treatment arms allocated in a 1:1 ratio.

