
#### Criteria for discontinuing or modifying allocated interventions {11b}

Changes in IMP dosing due to potential AEs will not be allowed. Decision to postpone or not administer a single IMP infusion (for example in case of adverse events or new contra-indication to administer IMP) or to discontinue further IMP treatment altogether will be made by the treating physician, if necessary, after deliberation with PI. Any changes in IMP regimen will be discussed with the coordinating PI prior to implementation and recorded as a protocol deviation.

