### Outcomes {12}

#### Primary outcome

The primary outcome is the number of patients in remission at 52 weeks after start of treatment. Remission is defined as sustained improvement without the need for further treatment. Improvement is defined as improvement by at least the minimal clinical important difference (MCID) on the inflammatory Rasch-Overall Disability Scale (I-RODS) and/or improvement of one or more points on the adjusted Inflammatory Neuropathy Cause and Treatment Disability Scale (INCAT-DS) at 18 weeks (end of treatment) compared to baseline. For the I-RODS, MCID is calculated using a statistical approach in which an increase of 1.96 SE is considered relevant improvement [12]. For the adjusted INCAT-DS, a decrease of 1 point or more is considered a relevant improvement [13, 14]. Changes in upper limb function from ‘0’ (normal) to ‘1’ (minor symptoms) or from ‘1’ to ‘0’ are not considered relevant deterioration or improvement [13]. Sustained is defined as no deterioration between 18 and 52 weeks, i.e. difference on the I-RODS of less than the MCID difference and/or less than one point on the adjusted INCAT-DS. Patients will be considered a treatment failure if they (1) received additional CIDP treatment during the 18-week intervention period, (2) do not improve at 18 weeks, (3) restart CIDP treatment for any reason between 18 and 52 weeks, or (4) do not show a sustained improvement at 52 weeks as defined above.

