### Sample size {14}

There are no robust figures on the long-term remission rates in patients treated with IVIg only. In a previous trial, remission during a 6-month period was seen in about half of IVIg responders, compared to 100% in IVMP responders [9]. However, a significant proportion of patients were not treatment naïve but known responders to IVIg. Furthermore, follow-up was shorter than the follow-up period in this study. We assume that the remission rate after IVIg is approximately 35% during an 8-month follow-up period. Treatment-naïve CIDP patients treated with dexamethasone had a long-term remission rate of 56% using a more stringent definition of improvement compared to this study [5, 8]. Our limited prospective pilot data of the OPTIC protocol suggest similar remission rates (59%) [10]. We assume remission rates of 35% in the IVIg/placebo group, and 65% in the IVIg/IVMP. A 30% difference in remission rate is large but warranted as IVMP may lead to various AEs in patients and because there is the alternative of continuing maintenance IVIg treatment. A two-group chi-square test with a 0.05 two-sided significance level will have 80% power to detect the difference between a control group proportion (IVIg/placebo) of 0.35 and a treatment group proportion (IVIg/IVMP) of 0.65 (odds ratio of 3.45) when the sample size in each group is 43 (86 patients in total). Anticipating on a 10% attrition rate due to AEs, we will include 48 (43/0.90) patients in each group (96 patients in total).

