### Statistical methods

#### Statistical methods for primary and secondary outcomes {20a}

Baseline assessments, outcome and safety parameters will be summarised using simple descriptive statistics. Continuous, normally distributed variables will be expressed as means and standard deviations; continuous, non-normally distributed and ordinal variables as medians (25th–75th percentiles); and categorical variables as counts and percentages. Normality of data will be explored by a Normal Q-Q Plot and tested by the Shapiro-Wilk test. Statistical uncertainties will be quantified with two-sided 95% confidence intervals. All analyses will be based on the intention-to-treat principle, whereas the primary outcome (the number of patients in remission) and three secondary outcomes (time to improvement on disability, number of patients with improvement on disability ≥ MCID, and number of (S)AEs) will be additionally analysed on per-protocol basis. A two-sided *p* value < 0.05 will be considered statistically significant. We will not correct for multiple testing. Data analyses will be performed blinded for the allocated study intervention.

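### The supportive per-protocol analyses of remission, improvement, time to improvement and (S)AEs drop some patients because of the outcome being analysed; ITT is unaffected

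*Protocol article*

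**What the plan says.** Section {20a} of the protocol article bases all analyses on intention to treat. It then adds a per-protocol analysis for remission and for three secondary outcomes: time to improvement, number of patients improved, "and number of (S)AEs) will be additionally analysed on per-protocol basis".

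Section {20c} defines the per-protocol set: "patients will be analysed who were included in accordance with the study protocol and who completed the treatment originally allocated". Protocol deviations exclude a patient apart from a short list: one missed IMP and/or IVIg administration, treatment up to 7 days out of window, and deviations within a single infusion.

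Other sections determine who fails that test:

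- Section {11b} lets the treating physician withhold or stop IMP, with adverse events as an example reason, and adds: "Any changes in IMP regimen will be discussed with the coordinating PI prior to implementation and recorded as a protocol deviation". Section {11d} likewise records IVIg changes as deviations.
- Participant timeline {13} stops trial medication if the regimen has to change during the 18 weeks, with follow-up continuing.
- The Primary outcome section makes a patient a treatment failure if they "received additional CIDP treatment during the 18-week intervention period". Section {17b} says the same of patients unblinded in that period so that treatment can be started or changed.

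No section keeps these patients in the per-protocol set.

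**The concern.** A per-protocol set is meant to describe what happens when the protocol is followed. Here, leaving the set can be a consequence of the outcome being counted.

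For (S)AEs, a patient who stops because of an adverse event and misses more than one administration has both a deviation and incomplete treatment. The event that caused the stop is then absent from the per-protocol count.

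For remission, a patient given additional CIDP treatment before week 18 already has a known result, failure, yet leaves the denominator. The same set serves the number improved and the time to improvement.

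These exclusions happen after randomisation and need not be equal between arms, so the comparison loses the protection of randomisation. At stake is how far the four per-protocol results can be read as support for ITT. Adverse events are a named secondary objective, and the Sample size section cites IVMP adverse events as one reason for requiring a large difference.

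**Working it through.** **The plan's own figures.** Inputs from Sample size {14} and Trial design {8}: "We assume remission rates of 35% in the IVIg/placebo group, and 65% in the IVIg/IVMP"; "A two-group chi-square test with a 0.05 two-sided significance level will have 80% power"; "two treatment arms allocated in a 1:1 ratio". With pooled variance and no continuity correction:

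n = [1.960 × √(2 × 0.5 × 0.5) + 0.842 × √(0.35 × 0.65 + 0.65 × 0.35)]² / 0.30² = 42.4, so 43 per group.

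Power at 43 is 80.6%. For attrition, 43/0.90 = 47.8, so 48. The odds ratio is (0.65/0.35)/(0.35/0.65) = 3.45. All stated figures reproduce, and none is disputed.

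**Who leaves the set.** The Primary outcome section gives four routes to failure.

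| Route | Treatment completed? | In per-protocol set? |
|---|---|---|
| Additional CIDP treatment in weeks 0 to 18 | No, trial medication is stopped | No |
| No improvement at week 18 | Can be complete | Yes, if complete |
| Restart in weeks 18 to 52 | Can be complete | Yes, if complete |
| Improvement not sustained at week 52 | Can be complete | Yes, if complete |

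Only the first route removes a patient because of failing. For adverse events, a patient who misses a single administration stays in; one who stops and misses more than one does not.

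**Remission.** Let p be an arm's ITT remission rate and f the share of the arm removed as early failures. None of those removed is in remission, so the per-protocol rate is p/(1 − f) and the odds are p/(1 − f − p). The documents do not give f; the values below are assumptions.

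| f control / IVMP | Control | IVMP | Difference | Odds ratio |
|---|---|---|---|---|
| none (ITT) | 35.0% | 65.0% | 30.0 points | 3.45 |
| 10% / 10% | 38.9% | 72.2% | 33.3 points | 4.09 |
| 10% / 20% | 38.9% | 81.2% | 42.4 points | 6.81 |
| 20% / 10% | 43.8% | 72.2% | 28.5 points | 3.34 |
| 30% / 10% | 50.0% | 72.2% | 22.2 points | 2.60 |

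With no true effect (50% in both arms), 10%/20% gives (0.5/0.3)/(0.5/0.4) = 1.33, and 20%/10% gives the reverse, 0.75.

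**Adverse events.** Let a be an arm's ITT share with the event and s the share that stops because of it and leaves the set. The per-protocol share is (a − s)/(1 − s). Assume 10% on control and 20% on IVMP, an excess of 10 points.

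- s = 0 on control, 10% on IVMP: 10.0% versus (0.20 − 0.10)/0.90 = 11.1%. The excess falls to 1.1 points.
- s = 2% and 10%: 0.08/0.98 = 8.2% versus 11.1%. The excess is 2.9 points.
- s = 5% in both arms: 0.05/0.95 = 5.3% versus 0.15/0.95 = 15.8%. The excess is 0.10/0.95 = 10.5 points, so it is not understated.

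The only figure in the article that bears on s is in Sample size {14}: "Anticipating on a 10% attrition rate due to AEs". That is 0.10 × 48 = 4.8, about 5 patients per arm. It is not split by arm and is not a forecast of per-protocol exclusions.

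**The case against.** The strongest reply is that nothing decisive rests on this set. ITT is the main analysis for both remission and (S)AEs, and it keeps every randomised patient whatever the deviation. The Safety evaluation section reports how many patients had (S)AEs leading to a change in or discontinuation of treatment. Events are recorded until 6 weeks after the last treatment in patients who stop early, and the DSMB reviews safety during the trial. Requiring completion with small tolerances is also a conventional per-protocol definition. All of this stands, and it confines the point to the supportive analyses. It does not repair them: a descriptive count of discontinuations does not correct a between-arm comparison made in completers.

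Two stronger readings are tempting. A reader might infer that the per-protocol safety comparison understates IVMP harm. The documents do not establish that. Both arms receive IVIg, IVIg changes for adverse events are also deviations, and no stopping rate by arm is given.

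A reader might also infer that the per-protocol remission result flatters IVMP. That is not established either. If 15% of control and 5% of IVMP patients leave as early failures, the rates are 0.35/0.85 = 41.2% and 0.65/0.95 = 68.4%. The odds ratio is then (0.65/0.30)/(0.35/0.50) = 3.10, slightly below 3.45.

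Nor does the set remove treatment failures in general; it removes only those whose allocated treatment ended early.

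**Conclusion.** The point holds for the supportive analyses. As written, the per-protocol set removes week 0 to 18 treatment failures from the efficacy analyses, and removes patients who stopped for an adverse event and missed more than one administration from the (S)AE analysis. In both cases the exclusion depends on the outcome. The ITT conclusions on efficacy and safety are untouched.

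The bias cannot be sized or signed from the documents. Both per-protocol remission rates rise when early failures are removed from both arms, but the odds ratio can move either way: from 3.45 to between 2.60 and 6.81 over the tabulated shares. An assumed 10-point AE excess on IVMP can shrink to about 1 point, but an excess is understated only if AE-related stopping is more frequent on IVMP. These results assume that every early failure and every patient who stopped for the event leaves the set, and that nobody else does.

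**What to change.** - **Section {20a}:** remove the number of (S)AEs from the outcomes analysed per protocol. Base safety conclusions on all randomised patients who started treatment. This is close to the existing ITT population, because patients who withdraw consent before treatment starts are already excluded under Handling of missing data.
- **Section {20c}:** in the per-protocol efficacy analyses, keep patients who received additional CIDP treatment or stopped for deterioration in weeks 0 to 18, and count them as failures. Exclude only for eligibility violations and for dosing deviations unrelated to outcome. For time to improvement, state how these patients' time is counted.

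The cost is rewording the analysis sets, with no new data and no change to patient management. The per-protocol set is then no longer a pure completer set, and its description should say so. The article reports 34 of 96 patients enrolled, and the code is in general broken only after database lock, so the change could be made before results by arm are known.

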##### Handling of missing data

Patients withdrawing consent after randomisation, but prior to the start of the treatment protocol, will be excluded from the analysis. In case the number of patients with missing data on the primary outcome is ≤ 1%, the primary outcome data will not be imputed. However, when the number of patients with missing values is larger than 1%, we will use multiple imputation with five imputed data sets to carry out the main analysis in the intention to treat population. We will use the imputed values for I-RODS and/or INCAT-DS to determine primary outcome if appropriate.

#### Plans to give access to the full protocol, participant-level data and statistical code {31c}

The protocol and generated datasets including statistical code are available from the corresponding author upon reasonable request.

### Composition of the data monitoring committee, its role and reporting structure {21a}

Monitoring and quality assurance of the study will be performed by monitors from the CRU of the Amsterdam UMC, location AMC, in compliance with GCP. Monitoring in the UK will be set up separately according to local and national requirements. Monitoring visits include an initiation visit, before enrolment of first subject and after ethics committee/institutional review board approval, and three monitoring visits followed by a closing visit after database lock. A monitoring plan is in place to guarantee adequate and uniform study monitoring and quality assurance. Monitors are given data viewing and query rights in the eCRF. Data collected throughout the study are monitored and the working forms, including questionnaires, are checked for accuracy and completeness. Queries are generated in the eCRF when questions arose during data checks. Queries are resolved within the requested timeframe and at least before the next site visit takes place. Safety reporting, including (S) AE reports and their proper administrative handling, will be checked for accuracy and completeness.

### Adverse event reporting and harms {22}

AEs are defined as any undesirable experience occurring to a patient during the first 24 weeks of the study (treatment period + 6 weeks), whether or not considered related to study drugs (IVMP, placebo), standard care (IVIg) or co-medication (osteoporosis prophylaxis). In case study treatment is stopped before the 18-week treatment protocol is completed (i.e. in case of deterioration, switch to plasmapheresis), (S) AEs are recorded until 6 weeks after last study treatment. All AEs reported spontaneously by the patient or observed by the investigator or his staff are recorded at each follow-up visit during the treatment period. In addition, we will use structured questionnaires to assess corticosteroid and IVIg-associated AEs at 18 weeks, 52 weeks and at 104 weeks (long-term safety follow-up). In case weight gain is reported and confirmed by investigator, an increase of 3 kg or more is considered an adverse event. A SAE is any untoward medical occurrence or effect that at any dose results in death, is life threatening (at the time of the event), requires hospitalisation or prolongation of existing inpatients’ hospitalisation, results in persistent or significant disability or incapacity and is a congenital anomaly or birth defect; any other important medical event that may not result in death, be life threatening, or require hospitalisation may be considered a serious adverse experience when, based upon appropriate medical judgement, the event may jeopardise the patient or may require an intervention to prevent one of the outcomes listed above. SAEs that occur during the first 24 weeks of the study, or in the case of an early endpoint within 6 weeks of last treatment course, whether or not causally related to the treatment with IVMP must be reported immediately (within 24 h of the investigator becoming aware of the event) to the sponsor. Hospitalisation for receiving IVIg or any other CIDP treatment, such as (admittance to a hospital/day care facility for) plasmapheresis, will not be regarded a SAE. The sponsor will report the SAEs through a specific web portal (ToetsingOnline) to the accredited METC that approved the protocol, within 15 days after the sponsor has first knowledge of the SAE. SAEs that result in death or are life threatening will be reported within 7 days after the responsible investigator has first knowledge of the adverse event. Complete report is reported within 8. SAEs that occur in the UK will be also reported in the UK following national and local regulations. All AEs will be followed until they have abated, or until a stable situation has been reached. Depending on the event, follow-up may require additional tests or medical procedures as indicated, and/or referral to the general physician or a medical specialist.

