#### Outcome measures

For disability, we will use the I-RODS and the INCAT-DS. The I-RODS is a patient self-report linearly weighted scale that measures activity and social participation limitations [12, 15]. The I-RODS consists of 24 questions and allows for three response options: (0) impossible to perform, (1) performed with difficulty and (2) easily performed. Scores range from ‘0’ (all activities impossible to perform) to ‘48’ (all activities easily performed). These scores are transformed and expressed in log-odds (logits), ranging from − 6.95 to 8.11. The I-RODS has been developed specifically for inflammatory neuropathies including CIDP and has been validated in a large group of patients [16]. In addition, disability will be measured using the adjusted INCAT-DS, which has been used in numerous CIDP trials [5, 13, 17]. The adjusted INCAT-DS is a 10-point ordinal scale measuring limb disability, ranging from ‘0’ (no arm or leg disability) to ‘10’ (no arm movement possible, wheelchair bound). The reason to choose both disability scales to assess improvement and remission is outlined in the discussion. We will use a handheld Vigorimeter to measure grip strength in kPa, the Medical Research Council (MRC) sum score of 12 predefined muscle groups (including shoulder abduction, elbow flexion, wrist extension, hip flexion, knee extension and foot dorsiflexion) to measure muscle strength, the INCAT- sensory sum score (INCAT-SS) to assess sensory impairment, the Rasch-built Fatigue Severity Scale (R-FSS), the Pain intensity numeric rating scale (PI-NRS) and the EuroQol (EQ-5D-5L) to measure HRQL [18–24]. Health care resources will be measured using working documents and the iMTA Medical Consumption Questionnaire (*i*MCQ) and the Productivity Cost Questionnaire (*i*PCQ), both adapted to the study population [25, 26]. Working documents keep track of IVIg use, outpatient hospital consultations, hospitalizations, and major diagnostic examinations and therapeutic interventions. Tailored *i*MCQ will be used to measure volume of out-of-hospital consultations (general physician, physical therapist, psychologist, etc.), other institutionalizations (temporary rehabilitation, nursing home), day-care treatment, emergency admissions and out-of-pocket expenses by patients. The impact of CIDP on the ability of a person to perform work, production loss following absence from work or personal inefficiencies will be measured with the *i*PCQ. AEs reported spontaneously at visits or otherwise reported by patient or observed by physician, during the first 24 weeks of the study, or in the case of an early endpoint during treatment protocol within 6 weeks of last treatment course, are recorded using an AE template provided by the Amsterdam UMC, Clinical Research Unit (CRU). The AE template consist of a description, severity score (mild, moderate, severe), potential relation to IMP (unlikely, unlikely, possible, probable, definite, not possible to assess), consequences for IMP administration (options including temporary or permanent stops, dose changes), any other actions taken (i.e. start of co-medication, a referral) and the outcome (i.e. resolved). Severity scores will be defined as followed: mild (i.e. an AE that is transient and may require only minimal treatment or therapeutic intervention; the event does not generally interfere with usual activities of daily living), moderate (i.e. alleviated with specific therapeutic intervention; the event interferes with usual activities of daily living, causing discomfort but poses no significant or permanent risk of harm to the research patient) or severe (i.e. an AE that interrupts usual activities of daily living, or significantly affects clinical status, or may require intensive therapeutic intervention). Patients will complete a structured questionnaire with most frequent corticosteroid and IVIg-related AEs at the 18-week visit. These AEs are subsequently scored by the investigator using the previously described severity score. (S)AEs are further described under the ‘Adverse event reporting and harms {22}’ section. Long-term corticosteroid related AEs are also assessed by the investigator at weeks 52 and 104. AE questionnaires are completed after all other outcome assessments have been performed. Patients are asked to indicate which treatment they think they have received, at the end of the study. Outcome measures and assessment visits are listed under the ‘Plans for assessment and collection of outcomes {18a}’ section and shown in Table 1.

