##### Safety evaluation

AEs reported or assessed during study visits in the first 24 weeks (or within 6 weeks in case of a preliminary endpoint) and AEs identified on patients’ questionnaires (week 18) will be summed up and plotted separately from adverse events reported on the physicians’ questionnaires (week 52). Frequency of (S) AEs, counted once per patient, as well as description, duration, severity score, consequences for IMP administration and outcome is summarised using descriptive statistics. Frequencies will be reported as counts (percentages), per treatment group. AEs are specified by description. Frequencies of patients reporting mild and moderate AEs (combined) and severe AEs are reported. For the physician completed week 52 AE questionnaire, frequencies of patients reporting AEs and specific AEs are reported. Frequencies will be compared between the treatment groups using the chi-square test. In case of low observed counts (< 10) or expected counts (< 5), we will use the Fischer exact test instead of the chi-square test. Frequency of SAEs along with description is reported. Frequency of patients with (S) AEs leading to change in or discontinuation of treatment protocol will be reported.

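### CIDP deterioration up to week 24 falls within the adverse event definition and can enter the pooled any-AE and severe-AE comparisons, diluting an excess of adverse events on IVMP

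*Protocol article*

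**What the plan says.** All references are to the protocol article.

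- **Definition and window** (Adverse event reporting and harms {22}). The section opens with this sentence: "AEs are defined as any undesirable experience occurring to a patient during the first 24 weeks of the study (treatment period + 6 weeks"). A link to study drug, IVIg or co-medication is not required. If study treatment stops early, for example because of deterioration, recording continues for six weeks after the last study treatment.
- **The one disease-related exception** (same section): "Hospitalisation for receiving IVIg or any other CIDP treatment" is not regarded as an SAE. This works at SAE level only and concerns the admission, not the worsening that led to it.
- **Severe grade** (Outcome measures): "an AE that interrupts usual activities of daily living, or significantly affects clinical status, or may require intensive therapeutic intervention".
- **Counting and testing** (Safety evaluation): "Frequency of (S) AEs, counted once per patient". Mild and moderate events are combined and severe events reported separately. "Frequencies will be compared between the treatment groups using the chi-square test", with Fisher's exact test for low counts. Events are also listed by description.
- **The same event as efficacy failure**: Provisions for post-trial care {30} and Primary outcome treat deterioration needing additional CIDP treatment in the 18-week period, and any restart of CIDP treatment in weeks 18 to 52, as a preliminary endpoint and a treatment failure.
- **Role of the comparison**: Objectives {7} makes more or fewer adverse events a secondary objective. Sample size {14} justifies the 30-point target partly by the adverse events IVMP may cause.

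**The concern.** The definition, window, grading, counting unit and test are all fixed in the article. Read together, they leave deterioration of the disease under study inside the harm outcome. Part of the efficacy result can then carry over into the safety comparison. If the combination works, the placebo arm has more deteriorations, its adverse event frequency rises more, and the observed excess on IVMP shrinks.

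The window runs six weeks beyond the last scheduled IVIg course, so it includes the first weeks in which patients can relapse off treatment. The trial must weigh a remission benefit against steroid harm, and a harm comparison partly offset by that same benefit is hard to read. The text also does not tell sites whether to enter a deterioration as an adverse event, so practice may differ between centres.

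**Working it through.** **The plan's own figure.** Sample size {14} states: "We assume remission rates of 35% in the IVIg/placebo group, and 65% in the IVIg/IVMP". With a pooled variance and no continuity correction, n = [1.96·√(2·0.5·0.5) + 0.842·√(0.35·0.65 + 0.65·0.35)]² / 0.30² = (1.386 + 0.568)² / 0.09 = 42.4, so 43 per group. Then 43/0.90 = 47.8, so 48 per group. Both stated figures reproduce, and 48 per arm is used below.

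**How many deteriorations fall in the window.** The document gives no early relapse rate. As an assumption, take every non-remission (65% placebo, 35% IVMP) to be a relapse in weeks 18 to 52. Weeks 18 to 24 are 6 of those 34 weeks, or 18%.
- Spread evenly: 0.65 × 6/34 = 11.5% and 0.35 × 6/34 = 6.2%.
- Constant hazard: 1 − 0.35^(6/34) = 16.9% and 1 − 0.65^(6/34) = 7.3%.

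**Formula.** With patients counted once and deterioration independent of other events, observed proportion = 1 − (1 − a)(1 − s·r). Here a is the proportion with an event other than CIDP deterioration, r the proportion deteriorating in the window, and s the share of deteriorations that enters the category (s = 1 for any AE). Power is exact, for the uncorrected two-sided 5% chi-square test.

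**Any AE, assumed 40% against 70%.**

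| In-window deterioration | Placebo | IVMP | Difference | Power |
|---|---|---|---|---|
| none counted | 40.0% | 70.0% | 30 points | 85% |
| 11.5% / 6.2% | 1 − 0.60·0.885 = 46.9% | 1 − 0.30·0.938 = 71.9% | 25 points | 71% |
| 16.9% / 7.3% | 1 − 0.60·0.831 = 50.1% | 1 − 0.30·0.927 = 72.2% | 22 points | 61% |

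**Severe AE, assumed 10% against 20%, with 11.5% / 6.2% deteriorating.** Only differences are given, because counts this low may trigger Fisher's test.
- Half graded severe: 1 − 0.90·(1 − 0.0575) = 15.2% and 1 − 0.80·(1 − 0.031) = 22.5%. The difference is 7.3 points, against a true 10.
- All graded severe: 1 − 0.90·0.885 = 20.4% and 1 − 0.80·0.938 = 25.0%. The difference is 4.6 points.

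**What a reversal would need.** Let k be the share of non-remitters who deteriorate by week 24. If all are graded severe, the difference is zero when 0.90(1 − 0.65k) = 0.80(1 − 0.35k), so k = 0.10/0.305 = 33%. At k = 50% the difference is −5 points. With half graded severe, it stays at +7.7, +5.0 and +2.4 points for k = 15%, 33% and 50%. The six-week window under even spread corresponds to k = 18%.

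**The case against.** The article never says that relapses are entered as adverse events. It treats deterioration throughout as an efficacy event, and coding rules for disease progression are often left to the full protocol, site instructions or analysis plan. A treated relapse fits the moderate grade at least as well as the severe one, since retreatment can follow a loss of one INCAT-DS point. Most relapses in weeks 18 to 52 fall after the window closes. Some non-remitters simply did not improve by week 18 and never deteriorated. Up to week 18 both arms receive IVIg, and no figure places early deteriorations mainly in the placebo arm. Events are listed by description, each record carries a relatedness score, and steroid-related events are assessed at weeks 18, 52 and 104. An all-cause count is also a legitimate summary of net harm, and removing deterioration from it could hide worsening caused by IVMP.

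Much of this stands and limits the size of the effect. A reader might infer that relapses will often be severe events and that steroid harm will be masked or even appear reversed. The document does not support that: it gives no severity rate, and for the severe-AE example above a reversal needs every deterioration graded severe and more than about a third of non-remitters deteriorating by week 24. The argument against full exclusion is also sound.

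The safeguards do not remove the problem. Listing by description shows the events but leaves them in the tested frequencies. The week-18 questionnaire events are summed with visit-reported events, and only the week-52 physician questionnaire is analysed apart. The admission exception protects the SAE count only in part, because a deterioration could still qualify through the disability criterion. Nor is the definition merely silent on detail: it covers any undesirable event, related or not, and deterioration plainly meets it.

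**Conclusion.** The point holds as one of dilution. Under the stated rules, CIDP deterioration up to week 24 can enter the pooled any-AE and severe-AE comparisons. If IVMP works as hypothesised, those comparisons understate its excess of adverse events. On the even-spread assumption the loss is about 5 of 30 points for any AE, and about 3 to 5 of 10 points for severe AEs, depending on whether half or all deteriorations are graded severe.

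These sizes rest on assumed adverse event rates, independence, and all non-remissions being relapses in weeks 18 to 52. The last assumption overstates the number in the window where failures are non-improvers, and leaves out any deterioration during treatment. The direction rests on the 52-week remission assumption, not on any stated early rate. The sample size and the primary analysis are unaffected.

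**What to change.** In Adverse event reporting and harms {22}, keep recording and expedited reporting as they are. Add a flag, set under blinding, to each AE or SAE that is a deterioration or relapse of CIDP, and say explicitly that such events are recorded. In Safety evaluation, tabulate the flagged events by arm and report the any-AE, mild/moderate, severe and SAE comparisons both with and without them. Showing both versions keeps the all-cause summary and leaves any worsening caused by IVMP visible.

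The cost is one blinded classification per event and one extra set of tables. Table 1 already schedules the I-RODS and INCAT-DS at unscheduled visits, which supports the classification. The article reports 34 of 96 patients enrolled and a randomisation code that is broken for the trial as a whole only after database lock, so the rule could still be set before comparative results are known.
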